**8. Study Design**

In phase II, participants will be followed months 0, 1, 2, 3, then 3 monthly with hematology and chemistry tests and laboratory evaluations of renal and hepatic function until 200 person-years of observation are accrued. At that point, a DSMB safety assessment will be conducted. Follow-up of enrolled participants will continue during the DSMB safety assessment. If safety is confirmed, all phase II participants will continue, and additional participants will be enrolled into the phase III portion of the trial. Enrollment of 2400 participants or accrual of 24 HIV infections (whichever comes first) is anticipated to take 36 months.

Participants will choose between two follow-up schedules: monthly (every 4 weeks) or monthly plus daily with directly observed therapy (DOT). During DOT visits clinic staff will witness the participant swallow his/her study medication and clinic staff will initial the participant’s tenofovir adherence card. Monthly visits will be the same for both groups and will include an assessment of tenofovir adherence and adverse events, a pill count and collection of unused pills, provision of a new 1 month supply of study medication, pre- and post-test HIV counseling, rapid oral HIV testing, urine pregnancy test (for female participants), HIV risk reduction counseling, and medication adherence counseling. At 0, 3, then 3 monthly visits, monthly procedures will be supplemented with a risk behavior questionnaire.

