**2. Protocol Summary**

**Title:** Study of the Safety and Efficacy of Daily Tenofovir to Prevent HIV Infection Among Injection Drug Users in Bangkok, Thailand (Bangkok Tenofovir Study)

**Objectives:** Primary objectives:

- To determine if daily oral tenofovir 300 mg prevents HIV infection among injection drug users (IDUs) in Thailand
- To determine if daily oral tenofovir 300 mg is safe when given to HIV-uninfected IDUs in Thailand

Secondary objectives:

- To evaluate changes in HIV associated risk behaviors during the trial
- To evaluate adherence of IDUs to daily tenofovir/placebo
  - - To determine if daily tenofovir is associated with a lower HIV viral load set point or higher CD4 count among trial participants who become HIV infected
    - To determine if tenofovir is associated with the development of antiretroviral resistance among trial participants who become HIV infected
    - To determine if the genetic characteristics of HIV viruses that infect placebo recipients differ from HIV viruses that infect tenofovir recipients

**Design:** A phase II/III, randomized, double-blind, placebo-controlled study of the efficacy and safety of oral tenofovir (tenofovir disoproxil fumarate) 300 mg administered once daily to HIV-uninfected IDUs.

In phase II, IDUs will be randomized 1:1 to once daily tenofovir or placebo until 200 person-years of observation have accrued when a data safety monitoring board (DSMB) safety review will be done. If safety is confirmed, all phase II participants will continue, and additional participants will be enrolled into the phase III trial until 2,400 persons have been enrolled. Participants will choose between daily follow-up with directly observed therapy (DOT) or monthly follow-up. Participants will remain on assigned study medication until 40 endpoints have accrued.

**Population:** HIV-uninfected Thai IDUs ages 20-60 years.

**Study Sites:** The study will be conducted at 17 Bangkok Metropolitan Administration (BMA) drug treatment clinics located in Bangkok, Thailand.

**Duration:** Phase II/III is estimated to take 48months; 36months to enroll 2,400participants, and an additional 12 months to complete follow-up.

**Test Products:** Tenofovir 300 mg or placebo.

**Study Procedures:** Interviews, risk reduction counseling, physical examinations, and/or laboratory evaluations at screening, enrollment, and every 4 weeks while on tenofovir or placebo.

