**7. Trial design**

This is a phase II/III, randomized, double-blind, placebo-controlled study of the safety and efficacy of chemoprophylactic tenofovir, administered orally once daily to IDUs. The study will be conducted in Bangkok at 17 BMA Drug Treatment Clinics. Study participants will be randomized (1:1) to receive tenofovir 300 mg or placebo. Participants will be evaluated for adverse events and HIV seroconversion.

The primary goals of this study are to assess the safety and efficacy of daily tenofovir to prevent parenteral HIV infection among IDUs. Assessment of changes in HIV associated risk behaviors, adherence to study drug, and, among IDU who become HIV-infected during the trial, evaluation of HIV viral load set point, CD4 counts, genetic characterization of infecting HIV viruses, and antiretroviral resistance will also be done.

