**13.1 Safety outcome**

Based on the AIDSVAX B/E vaccine trial, conducted 1999-2003 among IDUs enrolled from the same 17 BMA drug treatment clinics, we would expect a baseline SAE rate of about 7% during the year participants take study drug (Unpublished data). Assuming a sample size of 1000 per arm, table 3 shows the power to detect incremental increases in reported SAEs among tenofovir recipients compared to the placebo recipients using a 2-tail test and a 0.05 level of significance.

Table 3. Power to detect differences in reported SAEs among placebo and tenofovir recipients.

| Placebo Recipients | Tenofovir Recipients | Power |
| --- | --- | --- |
| 7% | 8% | 11% |
| 7% | 9% | 34% |
| 7% | 10% | 64% |
| 7% | 11% | 86% |
| 7% | 12% | 96% |
| 7% | 13% | 99% |

In summary, we have 80% power to detect an SAE rate above 11% among tenofovir recipients (4% greater than the 7% expected among placebo recipients).

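### The enrolment rule is stated in two ways, and Table 3 gives safety power for 1,000 per arm over one year instead of the planned 1,200 per arm on drug until 40 endpoints

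*Protocol*

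**What the plan says.** **Enrolment.** The Protocol Summary says that "additional participants will be enrolled into the phase III trial until 2,400 persons have been enrolled". Section 8 says: "Enrollment of 2400 participants or accrual of 24 HIV infections (whichever comes first) is anticipated to take 36 months". Section 13.10 places the interim efficacy analysis at about 24 seroconversions (60% of 40). No other section links 24 infections to the end of enrolment.

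**Exposure.** Section 7 states: "Study participants will be randomized (1:1) to receive tenofovir 300 mg or placebo". With 2,400 enrolled, that is 1,200 per arm. The Protocol Summary adds: "Participants will remain on assigned study medication until 40 endpoints have accrued". It plans 36 months of enrolment and "an additional 12 months to complete follow-up".

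**Safety power.** Section 13.1 states: "we would expect a baseline SAE rate of about 7% during the year participants take study drug". Table 3 is introduced with "Assuming a sample size of 1000 per arm", "using a 2-tail test and a 0.05 level of significance". It gives 11, 34, 64, 86, 96 and 99% power for 7% against 8, 9, 10, 11, 12 and 13%. Section 13.1 gives no reason for 1,000 instead of 1,200 per arm and states no allowance for loss.

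**The concern.** Read literally, sections 2 and 8 could lead staff or the DSMB to close enrolment at different times. In a sentence about enrolment, a whichever-comes-first condition has little meaning unless either event ends it.

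Safety is one of the two primary objectives in section 6.1, and Table 3 is its only power statement for the whole trial. It describes a trial with a fixed drug year, which this trial does not have. A DSMB or ethics committee reading it cannot tell what SAE excess the trial can detect, or that this depends on how fast HIV endpoints accrue.

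**Working it through.** **Step 1. Reproduce Table 3.** Inputs from section 13.1: 7% placebo rate, n = 1,000 per arm, two-sided 0.05. The method is a two-proportion normal approximation with continuity correction:

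- effective size n' = (n − 1/d)²/n, where d is the difference in proportions
- power = Φ{[d√n' − 1.96√(2p̄(1−p̄))] / √(p₁(1−p₁) + p₂(1−p₂))}

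For 7% v 11%, n' = 975²/1000 = 950.6. Power = Φ[(1.2333 − 0.7932)/0.4037] = Φ(1.09) = 86.2%. All six rows come to 11.6, 34.7, 64.3, 86.2, 96.3 and 99.3%, so Table 3 is right for its own inputs.

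**Step 2. Change only the arm size to 1,200.** n' = 1175²/1200 = 1150.5. Power = Φ[(1.3568 − 0.7932)/0.4037] = Φ(1.396) = 91.9%. For 7% v 10% it is 72.7%, against 64%.

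**Step 3. Exposure on the plan's own timeline.** Assume uniform accrual of 2,400 over 3 years (800 per year).

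- No loss: 2,400 × 1.5 + 2,400 × 1 = 6,000 PY, or 3,000 per arm.
- Loss as in the earlier cohort in section 5.1 (88.2, 75.9 and 71.2% at 12, 24 and 36 months; 66% at 48 months is my assumption): about 5,070 PY, or roughly 2,500 per arm.

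**Step 4. Power per person-year.** Power = Φ{ln(r₁/r₀)/√[1/(PY·r₀) + 1/(PY·r₁)] − 1.96}, with PY per arm. With 100 PY per arm this matches Table 5 within rounding, except for the row at relative rate 2.5 (53.5% here, 46% printed). For 7 v 10 per 100 PY, ln(10/7) = 0.3567:

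- 2,500 PY per arm: 0.3567/√(1/175 + 1/250) − 1.96 = 1.66, power 95%
- 3,000 PY per arm: 0.3567/√(1/210 + 1/300) − 1.96 = 2.00, power 98%

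Power of 80% is reached at about 9.3 and 9.1 per 100 PY respectively.

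**Step 5. Exposure when the trial ends at 40 endpoints.** Total PY = 40 / pooled incidence, with pooled incidence = placebo incidence × (2 − efficacy)/2. At 3.4 per 100 PY and 67% efficacy: 0.034 × 1.33/2 = 0.02261; 40/0.02261 = 1,769 PY, or 885 per arm. Under 800 per year and no loss:

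| | No 24-infection clause | Enrolment closed at 24 |
|---|---|---|
| Enrolled per arm | 841 | 652 |
| Month of 40th endpoint | 25.2 | 26.1 |
| PY per arm | 885 | 885 |
| Power, 7 v 11 per 100 PY | 79% | 79% |

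- Without the clause: √(1769/400) = 2.10 years, × 800 = 1,682 enrolled.
- With it: 24/0.02261 = 1,061 PY, reached at √(1061/400) = 1.63 years with 1,303 enrolled. The other 16 endpoints need 708 PY, which is 708/1303 = 0.54 year more.
- Power: 0.4520/√(1/61.95 + 1/97.35) − 1.96 = 0.82, which gives 79%.

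**Step 6. Range of incidence** (67% efficacy, same formulas, either enrolment rule):

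| Placebo incidence per 100 PY | PY per arm at 40 endpoints | Power, 7 v 11 | Power, 7 v 10 |
|---|---|---|---|
| 5.8 | 519 | 57% | 38% |
| 4.2 | 716 | 71% | 49% |
| 3.4 | 885 | 79% | 58% |
| 2.1 | 1,432 | 94% | 78% |
| 1.0 | 3,008 | >99% | 98% |

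The first four incidences are from section 5.1. The last is an assumption, close to what the 36 + 12 month timeline implies: 40/6,000 = 0.67 per 100 PY pooled, where the last row has 0.01 × 1.33/2 = 0.665.

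**The case against.** The strongest defence is that nothing here endangers safety. Table 3 is arithmetically sound and, for the fully enrolled design, conservative. The 1,000 is 83% of 1,200, which lies between the cited 12- and 24-month retention (88.2% and 75.9%), so it may be an unstated allowance for loss. One year matches the minimum commitment in section 8.2. Section 8 is worded as a forecast, and section 13.10 permits sample-size adjustment.

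Much of this stands, and it limits the point to a correction of stated figures. It does not explain the 1,000, which the protocol leaves unexplained. It does not turn drug use until 40 endpoints into a single year, and it does not reconcile the two enrolment rules.

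A reader might infer that closing enrolment at 24 infections would itself cut safety power. With 652 per arm, the one-year test for 7% v 11% gives 68%. The documents do not support that inference. It uses the one-year frame that does not fit the design and ignores that those participants would average 1,769/1,303 = 1.36 years. On a person-year basis, exposure is the same with or without the clause. Removing the clause would not restore 1,000 per arm either, since only about 841 are enrolled when the 40th endpoint arrives.

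Nor can 3.4 per 100 PY be taken as the only documented incidence. Section 5.1 also reports 5.8 in the earlier cohort and a range of 2.1 to 4.2 within the vaccine trial, and section 13.2 suspects a decline without giving a figure.

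**Conclusion.** The point holds as an inconsistency plus a power table for the wrong design. Two enrolment rules stand in current text. For 2,400 enrolled on the stated timeline, Table 3 understates power: 92% against 86% for 7% v 11% from arm size alone, and about 95 to 98% against 64% for the 7 v 10 comparison once exposure is counted.

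That direction is not guaranteed. Endpoint-driven exposure falls as incidence rises, and at 3.4 per 100 PY with 67% efficacy power for 7 v 11 per 100 PY is about 79%, just below the 80% in the section 13.1 summary. What drives this is incidence, not the 24-infection clause.

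The figures assume uniform accrual, constant HIV and SAE rates, and SAEs treated as independent events. The equality of the two rules in Step 5 rests on constant incidence; its calendar times and enrolment numbers also assume no loss. The correction should be made, but it gives no reason to doubt that the trial can meet its safety objective at the incidence its timeline implies.

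**What to change.** 1. State one enrolment rule in the Protocol Summary and section 8. Unless a cap is intended, leave 24 infections as the interim trigger only. If a cap is intended, write it in both places.
2. In section 13.1, remove the wording that ties the 7% SAE rate to a single year on drug.
3. Restate Table 3 as SAE rates per person-year, as Table 5 already does, for the actual number enrolled, an explicit allowance for loss, and the exposure expected at 40 endpoints over a range of HIV incidence. Revise the summary sentence below the table to match.

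The cost is a few words and one recalculated table. The planned 2,400, the 40-endpoint target and the interim analysis do not change.

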**8.1 Study population**

The population to be included in this study is IDUs in Bangkok.

**8.1.1 Recruitment**

IDUs seeking treatment at BMA drug treatment clinics will be offered HIV counseling and testing and screening for the tenofovir study. Subjects may be recruited from existing IDU cohorts (e.g., the AIDSVAX B/E Extension Study [CDC #3750]). In addition, an IDU peer referral program will be conducted.

**8.2 Inclusion criteria**

- 20-60 years of age
- Report injection drug use in the 12 months before screening
- Possess documentation of Thai National Identification number
- Laboratory values as follows within 2 weeks before enrollment:
  - HIV oral fluid test non-reactive at screening and pre-enrollment visits
  - Hemoglobin  9 gm/dL
  - ALT and AST  2.5 x upper limit of normal (ULN)
  - Total bilirubin  1.5 mg/dL
  - Serum amylase  1.5 x ULN
  - Serum phosphorus 2.2 mg/dL
  - No evidence of current or chronic Hepatitis B infection by serology
  - Calculated creatinine clearance 60 mL/min by the Cockcroft-Gault formula where creatinine clearance in mL/min =

Male: (140 – age in years) x (wt in kg)

72 x (serum creatinine in mg/dL)

Female: (140 – age in years) x (wt in kg) x 0.85

72 x (serum creatinine in mg/dL)

- Willing to abstain from sexual intercourse or use effective contraception during the trial (oral, injection, or barrier) (women)
- Pass the comprehension test
- Willing and able to provide informed consent for study participation
- Available and committed to DOT or monthly follow-upfor at least 12 months

**8.3 Exclusion criteria**

- - Clinic physicians will determine if a subject with chronic illness requiring prescription medication can not enroll (medication used for drug treatment is allowed)
  - Positive urine pregnancy test (women)
  - Breastfeeding (women)
  - History of significant renal, liver, or bone disease
  - Any other clinical condition or prior therapy that, in the opinion of the clinic physician, would make the subject unsuitable for the study or unable to comply with the dosing requirements
  - Concurrent participation in any other HIV prevention trial or drug/vaccine safety trial. AIDSVAX B/E HIV vaccine trial (CDC protocol #2076) participants and Extension Study (CDC protocol #3750) participants may be screened for enrollment in the Bangkok Tenofovir Study.

**8.4 Participant retention**

Study staff will make every effort to retain participants for the duration of the trial to minimize possible bias associated with participant loss-to-follow-up. Components of retention procedures will include:

- A comprehension test administered to each potential participant to assess their understanding of the trial; subjects must pass the test in order to enroll
- A thorough explanation of the study visit schedule and procedures during the informed consent process and re-emphasis at each study visit
- Collection of locator information during screening/enrollment and at each study visit
- Use of appropriate and timely visit reminder mechanisms (e.g., appointment calendar, phone, post cards)
- Follow-up of missed visits by clinic staff as described in the informed consent (e.g., phone call, post card, home visit)
- BMA will coordinate with appropriate authorities (e.g., Ministry of Justice, Police Department) to allow follow-up of incarcerated study participants

**8.5 Participant withdrawal**

Participants may withdraw from the study for any reason at any time. The Principal Investigator also may withdraw participants from the study to protect the participant’s health and/or if the participant is unwilling or unable to comply with required study procedures. Such reasons include, but are not limited to, grade 4 creatinine elevation or grade 3 with recurrence, pregnancy, or the onset of health conditions that compromise study participation. Participants may also be withdrawn if the study sponsor, the BMA, the Royal Thai Government, or regulatory authorities terminate the study prior to its planned end date.

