**10.3.4 Exit visit (Study completion, HIV infection confirmation visit, early termination)**

Clinic staff will conduct all the monthly and 3-monthly procedures. In addition, a blood specimen will be collected and a physical examination done.

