**11.8 Management of pregnancy after study enrollment**

Women who become pregnant during the study will stop taking study drug and be withdrawn from the study. Prenatal care will not be provided by the study, but women will be assisted with antenatal care arrangements. In addition, women who become pregnant will be offered immediate voluntary HIV counseling and testing. Women testing positive for HIV will be referred and encouraged to participate in BMA ‘prevention of mother to child transmission’ services. After obtaining participant consent, clinic staff will review the medical record of delivery to assess maternal and newborn health. Pregnancy data and pregnancy outcomes will be reported to the Antiretroviral Pregnancy Registry ([contact], [contact], [contact]).

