**12.8.1 Management of laboratory abnormality *(except serum creatinine elevation)* or clinical event**

**Grade 1 or 2:** Continue study medication at the discretion of the study physician.

**Grade 3 or 4:** May continue study medication, at the discretion of the study physician, for up to 3 days while values are confirmed.

**Confirmed grade 3:** If unrelated to study drug by above definitions, may continue dosing. If causal relationship to study drug possible by above definitions, withhold drug until toxicity returns to < grade 3 then retest to confirm participant is HIV negative then restart study drug. If toxicity > grade 3 recurs, permanently discontinue dosing and follow at scheduled study visits until toxicity resolves.

**Confirmed grade 4:** If unrelated to study drug by above definitions, may continue dosing. If causal relationship to study drug possible by above definitions, permanently discontinue study drug and follow at scheduled study visits until toxicity resolves. Do not rechallenge.

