**13.7 Analysis plan summary**

All randomized patients will be included in the analysis. The analysis will be performed on an intention-to-treat basis. Data from participants lost to follow-up will be censored at the last contact. To assess the success of randomization, a summary of baseline variables by study arm will be tabulated. Continuous data will be summarized with descriptive statistics, including n, mean, standard deviation, minimum, maximum, median and interquartile range. Categorical data will be summarized using counts and percents. A significance level alpha=0.05 will be used to perform significance testing and construct confidence intervals. Heterogeneously distributed variables will be regarded as potential confounders and will be adjusted for in multivariable modeling. Missing data will be summarized by treatment groups, and missing patterns will be assessed using graphical and modeling approaches and an appropriate multiple imputation technique will be applied.24 All analyses will be done using SAS version V8 (Cary, NC, U.S).

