**13.9 Efficacy analysis**

The study hypothesis is that HIV incidence will be lower among participants receiving tenofovir than among participants receiving placebo. A log-rank statistic will be used to test the efficacy of treatment.25 The efficacy of treatment will be estimated as

Efficacy = 1 – *RR*

where *RR* is the hazard ratio estimated from a discrete time proportional hazards regression model with an indicator variable representing treatment arm. Confidence intervals for efficacy can be calculated using the confidence limits for the *RR*.

All analyses will be performed on an intention-to-treat basis. Rates of HIV seroconversion with Poisson 95% exact confidence intervals will be used to summarize the data. Discrete time proportional hazards regression will be applied to adjust the treatment effect for age and gender and for other demographic or behavioral variables, which, despite the randomization, were heterogeneously distributed between the study arms.

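### Withdrawal from the study, as distinct from stopping study drug, ends HIV follow-up for reasons tied to compliance, tolerability or health, which departs from the declared intention-to-treat analysis; last contact is also the wrong censoring date

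*Protocol*

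**What the plan says.** **Leaving the study.** Section 8.5 allows the Principal Investigator to withdraw a participant from the study to protect the participant's health or "if the participant is unwilling or unable to comply with required study procedures". The reasons named, in a list that is expressly not exhaustive, are "grade 4 creatinine elevation or grade 3 with recurrence, pregnancy, or the onset of health conditions that compromise study participation". For pregnancy there is no discretion: under section 11.8 such women "will stop taking study drug and be withdrawn from the study".

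**What follows.** Section 10.3.4 groups early termination with the other exits: "Exit visit (Study completion, HIV infection confirmation visit, early termination"). Table 2 includes an HIV test at that visit. Section 11.8 adds an immediate offer of HIV testing in pregnancy and a later review of the delivery record. No schedule of HIV tests after withdrawal is described. The follow-up schedule in section 10.3.5 is for newly infected participants.

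**Stopping drug for toxicity.** For a confirmed grade 4 event possibly related to drug, section 12.8.1 says "permanently discontinue study drug and follow at scheduled study visits until toxicity resolves". Section 12.8.2 ties monitoring to serum creatinine returning to normal. Neither says whether HIV follow-up continues afterwards.

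**Analysis.** Section 13.7 includes all randomized patients and adds: "Data from participants lost to follow-up will be censored at the last contact". Section 13.9 states: "All analyses will be performed on an intention-to-treat basis".

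**The concern.** An intention-to-treat comparison of time to infection needs HIV status in everyone randomized up to the common end of follow-up, on or off drug. Listing everyone in the analysis set is not enough: the log-rank test and the discrete-time hazard model receive no time and no events after withdrawal.

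The reasons for withdrawal are not neutral. Poor compliance with procedures may go with higher infection risk, and tolerability may depend on the treatment received. Censoring for such reasons can be informative. What is lost is a set of HIV tests never taken, so no statistical analysis plan could restore it. Section 13.2 set its 10% efficacy threshold so that the result could guide public health action, and for that purpose the effect that includes people who come off drug matters.

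The censoring date is a second, smaller matter. HIV-free status is known only up to the last negative test. If a later contact without a test sets the date, the time between is counted as infection-free.

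**Working it through.** **1. The plan's own figure.** Section 13.2 gives 82% power at 40 endpoints and 67% efficacy to put the lower 95% limit of efficacy above 10%, that is, the upper limit of the hazard ratio (HR) below 0.90. Given 40 events and 1:1 allocation, tenofovir events are approximately Binomial(40, p) with p = HR/(1 + HR). With x tenofovir events, the upper limit is exp[ln(x/(40 − x)) + 1.96·√(1/x + 1/(40 − x))], which gives 0.843 at x = 12 and 0.933 at x = 13. Success therefore means x ≤ 12.

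- HR = 1/3 (the table's 10/30 split): p = 0.25, P(x ≤ 12) = 82.1%.
- HR = 0.33: p = 0.248, P(x ≤ 12) = 82.8%.

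The stated 82% reproduces. No printed number is in error; the issue is which effect the data will support.

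**2. What unobserved time could hide.** Let f be the share of tenofovir-arm person-time lost after withdrawal, and assume that this time is off drug at placebo risk. Had it been observed:

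HR(ITT) = 0.33(1 − f) + f, so efficacy = 0.67(1 − f).

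| f (assumed) | HR(ITT) | ITT efficacy | Power at 40 events |
|---|---|---|---|
| 0 | 0.330 | 67.0% | 82.8% |
| 3% | 0.350 | 65.0% | 78.2% |
| 10% | 0.397 | 60.3% | 66.2% |

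The protocol states no f. The 3% row uses an order of magnitude from Table 1 in section 9.1.3: over 24 weeks, clinical events led to permanent drug discontinuation in 3% on tenofovir and 2% on placebo, and laboratory events in 0 and 2%. Those are HIV-infected, treatment-experienced patients stopping drug, not withdrawals from this study. The 10% row has no source in the document. Section 5.1 reports 12-month retention of 88.2% in an earlier cohort, but that is ordinary attrition, not investigator withdrawal. Pregnancy probably adds little, since 94.3% of those screened for the earlier vaccine trial were male (section 5.1).

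**3. Which contacts carry an HIV test.** Table 2 places OraQuick testing at screening, enrollment, monthly, 3-monthly, exit and post-analysis visits. In the daily-visit column the only entry is the adherence diary review. Section 8.4 follows up missed visits by phone call, post card or home visit. Last contact can therefore fall after the last test.

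**4. Size of the untested time.** Even enrollment of 2,400 over 36 months with 12 months more gives a mean of 18 + 12 = 30 months, or 2,400 × 2.5 = 6,000 person-years before any loss. Assume that 25% are lost (section 5.1 implies 24.1% at 24 months in the earlier cohort) with 1 to 3 months between last test and last contact. Then 2,400 × 0.25 × (1 to 3)/12 = 50 to 150 person-years, which is 0.8% to 2.5% of the total. The gap of 1 to 3 months is an assumption. If a share u of time is untested in both arms, each arm's observed incidence is its true value times (1 − u), and the ratio of the two is unchanged.

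**The case against.** The strongest reply is that most people off drug are meant to stay in the trial. Section 9.6 provides for interruption, re-testing and restart. Section 9.5 measures non-adherence in retained participants. Section 10.3.6 asks those without drug or unable to take it to come back to the clinic. Withdrawal under 8.5 is discretionary, refers to study procedures and not to missed doses, and is decided under blinding. Section 13.7 also plans to examine missing-data patterns by arm and to apply multiple imputation. All of this stands, and it rules out several stronger readings that a reader might draw:

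- **That the plan censors at drug discontinuation and so becomes a partly on-treatment analysis.** No rule says so.
- **That sections 12.8.1 and 12.8.2 end participation.** They give drug-stopping and monitoring instructions and are silent on HIV follow-up after the toxicity resolves.
- **That off-drug time is removed selectively from the tenofovir arm.** The document gives no withdrawal rates by arm, and Table 1 shows no overall excess of discontinuation on tenofovir.
- **That the trial would still report about 67% whatever happened off drug.** This would need all off-drug time to be censored.
- **That the type I error is inflated by a known amount.** Any figure needs an assumed excess of high-risk withdrawals on tenofovir.

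Two more points are fair. The last-contact sentence is worded for loss to follow-up, so applying it to withdrawals is an inference. A withdrawn participant who attends the exit visit is tested there. The exact handling of censoring could also be left to a statistical analysis plan. None of this supplies HIV tests after withdrawal, however, and imputation is not tied to the HIV endpoint or to withdrawn participants.

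**Conclusion.** The point holds in a limited form. The protocol permits withdrawal from the study itself for reasons linked to compliance, tolerability or health, requires it for pregnancy, and describes no scheduled HIV testing afterwards. That departs from the declared intention-to-treat analysis and can make censoring informative. For toxicity stops under 12.8 the protocol leaves the question open and does not answer it wrongly.

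Direction and size cannot be determined. The figures of 65% and 60% against 67% rest on assumed shares of 3% and 10%, placebo risk after withdrawal and 67% efficacy on drug. They show sensitivity and do not estimate bias in this trial. The last-contact rule is a separate, minor fault: under the stated assumptions it understates incidence by about 1% to 2.5%, with little effect on the hazard ratio if the gap is similar in both arms.

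**What to change.** - **Sections 8.5, 11.8 and 12.8:** state that stopping study drug does not end study participation, and that anyone off drug continues HIV testing on the existing schedule to the common end date unless consent is withdrawn. The rules on when drug is stopped do not change.
- **Section 13.7:** for the efficacy endpoint, censor at the last negative HIV test instead of at last contact.

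The cost is a short amendment and some extra HIV-test visits for the minority off drug. The intention-to-treat estimate may come out smaller. If so, power at 40 events would fall with it, as in the illustration above (82.8% to 78.2% or 66.2%), but the result would match the analysis that the protocol declares.
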